# Effects of individualized PEEP obtained by two different titration methods on postoperative atelectasis in obese patients: study protocol for a randomized controlled trial

**DOI:** 10.1186/s13063-021-05671-1

**Published:** 2021-10-15

**Keywords:** Obesity, Individualized PEEP, Cstat, Electrical impedance tomography, Atelectasis

## Abstract

**Background:**

The incidence of postoperative pulmonary complications (PPCs) is higher in obese patients undergoing general anesthesia and mechanical ventilation due to the reduction of oxygen reserve, functional residual capacity, and lung compliance. Individualized positive end-expiratory pressure (iPEEP) along with other lung-protective strategies is effective in alleviating postoperative atelectasis. Here, we compared the best static lung compliance (Cstat) titration of iPEEP with electrical impedance tomography (EIT) titration to observe their effects on postoperative atelectasis in obese patients undergoing laparoscopic surgery.

**Methods:**

A total number of 140 obese patients with BMI ≥ 32.5kg/m^2^ undergoing elective laparoscopic gastric volume reduction and at moderate to high risk of developing PPCs will be enrolled and randomized into the optimal static lung compliance-directed iPEEP group and EIT titration iPEEP group. The primary endpoint will be pulmonary atelectasis measured and calculated by EIT immediately after extubation and 2 h after surgery. Secondary endpoints will be intraoperative oxygenation index, organ dysfunction, incidence of PPCs, hospital expenses, and length of hospital stay.

**Discussion:**

Many iPEEP titration methods effective for normal weight patients may not be appropriate for obese patients. Although EIT-guided iPEEP titration is effective in obese patients, its high price and complexity limit its application in many clinical facilities. This trial will test the efficacy of iPEEP via the optimal static lung compliance-guided titration procedure by comparing it with EIT-guided PEEP titration. The results of this trial will provide a feasible and convenient method for anesthesiologists to set individualized PEEP for obese patients during laparoscopic surgery.

**Trial registration:**

ClinicalTrials.govChiCTR2000039144. Registered on October 19, 2020

**Supplementary Information:**

The online version contains supplementary material available at 10.1186/s13063-021-05671-1.

## Background

The incidence of postoperative pulmonary complications (PPCs) in obese patients is as high as 18%, which is almost twice that in normal weight or overweight patients [1, 2]. It is widely acknowledged that PPCs cause a significant increase in morbidity and mortality, prolonged length of hospital stay and ICU stay, and increased treatment expenses [2, 3]. Considering that roughly 310 million patients undergo surgery worldwide annually [4], reducing the rate of PPCs should have a positive impact on mortality and morbidity. It could also improve patients’ prognosis and reduce health system expenses.

According to an international expert consensus [5], lung-protective ventilation strategies including low tidal volume [6], recruitment maneuvers, individualized PEEP, and the lowest possible oxygen concentration have been associated with reduced incidence of postoperative pulmonary complications. Among these, individualized PEEP plays an important role in preventing processive alveolar collapse; however, no agreement has been reached about how to select individualized PEEP.

Patients whose BMI equal to or exceed 35 kg/m^2^ are more susceptible to developing PPCs compared with mild obese and normal weight patients. In obese patients, respiratory function is undermined due to the decreased oxygen reserve, respiratory compliance, and functional residual capacity [7]. Moreover, obese patients are prone to develop atelectasis, which is further exacerbated by general anesthesia and mechanical ventilation. When obese patients undergo laparoscopic surgery, the cephalic shift of diaphragm and elevated pleural pressure imposed by pneumoperitoneum increase the proportion of atelectatic lung tissue. An intraoperative higher level of PEEP with alveolar recruitment maneuvers may improve respiratory function in obese patients [7, 8].

Recently, PROBESE trial, an international randomized trial, using a higher level of PEEP (12 cmH_2_O) and ARM compared with a lower level of PEEP (4 cmH_2_O) in obese patients, did not reduce PPCs [1, 9]. The conclusion of this study was not consistent with previous studies [7, 8]. However, the lack of individual titration of PEEP is their major limitation [1]. Nestler and his colleagues [8] revealed that in obese patients undergoing elective laparoscopic surgery, compared to patients ventilated with a fixed PEEP of 5 cmH_2_O, patients ventilated with individualized PEEP titrated through an electrical impedance tomography (EIT)-guided procedure experience alleviated atelectasis, improved regional ventilation distribution and oxygenation, and decreased driving pressure. Therefore, for obese patients, the appropriate individual PEEP rather than a single high level of PEEP may be more beneficial. However, the EIT instrument is expensive, making it unavailable for many medical institutions. In some thoracic and abdominal operations, the scope of disinfection also limits its application. The complex techniques related to EIT further impair its feasibility in routine clinical practice. Therefore, some simple and highly feasible methods to titrate individualized PEEP for obese patients need to be found out.

This trial is going to verify the hypothesis: individualized PEEP titrated by optimal static lung compliance (Cstat) in combination with other lung-protective ventilation strategies is not inferior to individualized PEEP titrated via EIT in terms of reducing atelectasis, improving oxygenation and reducing the incidence of PPCs in obese patients at moderate to high risk of developing PPCs.

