Oxygenation index: At before intubation (T0), after the third RM and before extubation (T1), arterial blood is drawn, blood gas analysis is performed, and oxygenation index is calculated.Respiratory parameters: Every 5 min, RR, VT, Ppeak, Pplat, and PEEP are recorded.Blood gas analysis indicators: At before intubation (T0), after the third RM and before extubation (T1), arterial blood is drawn and blood gas analysis is performed.Anesthesia-associated parameters: hemodynamic parameters, recovery time, anesthetic dosage, and occurrence of hypoxemia are recorded constantly.Tertiary outcomes: length of ICU stay, length of hospital stay, costs of treatment, postoperative complications, and other adverse events are recorded.We define PPCs as follows:Mild respiratory failure: PaO_2_/FiO_2_ < 300 or SpO_2_<90%, measured after at least 10 min of breathing room air, but could be alleviated by inhaling supplementary oxygen of 2L/min, hypoventilation excluded.Moderate respiratory failure: PaO_2_/FiO_2_ < 300 or SpO_2_<90%, measured after at least 10 min of breathing room air, but could be alleviated only by inhaling supplementary oxygen>2L/min, hypoventilation excluded.Severe respiratory failure: requiring noninvasive or invasive mechanical ventilation, excluding hypoventilation due to the use of narcotics.ARDS (according to Berlin definition).Bronchospasm (newly detected expiratory wheezing, responding to bronchodilators).New pulmonary infiltrates (new monolateral or bilateral infiltrates demonstrated by chest X-ray, without other clinical signs.)Pulmonary infection (new or progressive radiographic infiltrate plus at least two of the following: requirement of antibiotic treatment, tympanic temperature >38°C, leukocytosis, or leukopenia [white blood cell count <4000 cells/mm^3^ or > 12,000 cells/mm^3^], and/or purulent sputum).Aspiration pneumonitis (respiratory failure resulting from inhalation of regurgitated gastric contents).Pleural effusion (one of the following demonstrated by chest X-ray: blunting of the costophrenic angle, loss of the sharp silhouette of the ipsilateral hemidiaphragm in the upright position, evidence of adjacent anatomical structures displacement, or [in supine position] a hazy opacity in one hemithorax with preserved vascular shadows).Atelectasis (lung opacities with a shift of the hilum, mediastinum, or hemidiaphragm toward the affected area, along with compensatory overdistension in the adjacent nonatelectatic lung).Cardiopulmonary edema (clinical signs of congestion, including dyspnea, edema, rales, and jugular venous distention, with chest X-ray demonstrating an increase in vascular markings and diffuse alveolar interstitial infiltrates).Pneumothorax (air in the pleural cavity, without vascular bed around the visceral pleura).

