### Sample size calculations

The primary endpoint of this study is the ratio of collapsed lung mass to normal lung tissue, which is measured and automatically calculated via using EIT before anesthesia and immediately after endotracheal extubation. According to our pre-experimental results of this study, the lung collapse area in the Cstat-PEEP group was 6.5%, while that in the EIT-PEEP group was 6.2%. We apply a noninferiority test. We hypothesize that compared with the ratio of lung collapse area in the EIT-PEEP group, the ratio of lung collapse area in the Cstat-PEEP group will increase by no more than 2% (i.e., the ratio of lung collapse area in Cstat-PEEP group within 8.2% is non-inferior). We choose a two-sided significance level of 0.025 (*α*) and *β*= 0.2, with a power of 80%. Using the PASS 11.0 software, a sample size of 64 is calculated for each group. Taking a 10% dropout rate in patients’ follow-up into account, a final sample size of 70 is required for each group.

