## Discussion

This trial is sufficiently powered to test the hypothesis that an individualized PEEP titrated by maximizing Cstat is not inferior to individualized PEEP determined by EIT in terms of lowering the proportion of collapsed lung tissue, for obese patients. The result will prove that the method of best Cstat titration iPEEP is simple and effective in clinical practice.

According to a population-based study, in 2014, approximately 10.8% of men and 14.9% of women are obese globally [13]. In obese patients, the respiratory compliance is further limited by the cephalic movement of the diaphragm. In addition, the FRC and alveolar ventilation volume of obese patients are much lower than their non-obese counterparts. The incidence of atelectasis in obese patients under general anesthesia is as high as 90% [14]. In obese patients under general anesthesia and mechanical ventilation, the proportion of normal ventilated lung tissue drops from 71 to 50%, while the proportion of insufficiently ventilated lung mass increases from 28 to 39%, and the proportion of non-ventilated lung tissue elevates from 1 to 11%. In sharp contrast, the proportion of atelectatic lung mass is only 3% in normal weight patients under general anesthesia and mechanical ventilation [15].

Because airway pressure required to keep lung units from collapsing is much lower than the pressure needed to recruit atelectatic lung units, recruitment maneuver could significantly improve ventilation. Applying PEEP after a successful recruitment maneuver could prevent the rapid reformation of atelectasis, especially when the fraction of inspired oxygen is as high as 100% [16]. Applying PEEP alone alleviates the reduction of end-expiratory lung volume and lung elastance imposed by pneumoperitoneum on obese patients, but fails to reduce an atelectatic fraction of the lung tissue [17]. Compared to PEEP applied alone, the combination of PEEP and recruitment maneuver leads to greater enhancement in lung elastance and results in lower airway pressure as well as resistance in obese patients undergoing laparoscopic surgery.

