In conclusion, this study aims to verify the following hypothesis: individualized iPEEP titrated to optimal static lung compliance is not inferior to individualized iPEEP obtained during a titration procedure guided by EIT, in terms of improving intraoperative oxygenation and ameliorating postoperative atelectasis in obese patients undergoing laparoscopic surgery. This study will provide a convenient and feasible strategy for individualized PEEP titration in obese patients. The result shall provide direct evidence to further refine lung-protective ventilation strategies in obese patients and exploit the significance of lung-protective ventilation in ERAS in obese patients.

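### The Background and Discussion claim non-inferiority on oxygenation (and, in the Background, pulmonary complications), but only lung collapse has a margin and a sample size

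*Protocol article*

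**What the plan says.** The Protocol article states its non-inferiority hypothesis three times, with a different scope each time.

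- **Background, last paragraph:** Cstat titration is not inferior to EIT titration "in terms of reducing atelectasis, improving oxygenation and reducing the incidence of PPCs" (three outcomes).
- **Discussion, last paragraph before Trial status:** not inferior "in terms of improving intraoperative oxygenation and ameliorating postoperative atelectasis" (two outcomes; PPCs are gone).
- **Discussion, first paragraph:** the trial is said to have enough power to show non-inferiority "in terms of lowering the proportion of collapsed lung tissue" (one outcome).

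Sample size calculations applies a non-inferiority test to lung collapse only. The hypothesis there is that "the ratio of lung collapse area in the Cstat-PEEP group will increase by no more than 2" percent, that is, from 6.2% to at most 8.2%. The result is 64 per group, raised to 70. No margin, assumed rate or SD is given for oxygenation or PPCs.

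Statistical analysis lists the unpaired t test, Mann-Whitney, Fisher, chi-square and relative risk, with P<0.05 as significant. It also plans 95% CIs but compares them with no margin.

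The rank of PPCs varies too. The Abstract says "Secondary endpoints will be intraoperative oxygenation index, organ dysfunction, incidence of PPCs", whereas Study endpoints has "Tertiary outcomes: length of ICU stay, length of hospital stay, costs of treatment, postoperative complications", with the PPC definition following in the same list.

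**The concern.** A non-inferiority hypothesis needs a margin. Without one, no result can confirm or refute it. The Background and the closing Discussion therefore commit the trial to claims on oxygenation, and in the Background also on PPCs, that the rest of the article gives no means of testing.

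The listed tests ask whether the arms differ. Failing to show a difference does not exclude a relevant excess in the Cstat arm, least of all for a binary outcome in a trial of this size. Because the trial is meant to justify a simpler substitute for EIT, a statement that PPCs were not inferior would carry clinical weight that the data could not support.

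**Working it through.** **Inputs from the article.** Margin 2 points for collapse; pilot means 6.5% (Cstat) and 6.2% (EIT); power 80%; 64 evaluable per group, 70 randomised per group. The Background says the incidence of PPCs "in obese patients is as high as 18" percent.

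**Assumptions made here.** The article sets no PPC planning rate, so 18% in both arms is an assumption, with 10% as a lower alternative. The PPC margins below are also assumptions. One-sided α is 0.025, which matches a 95% CI, so z = 1.96 + 0.8416 = 2.8016. Reading the article's two-sided 0.025 literally would only enlarge the testable margins.

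**1. The plan's own figure.** The 64 cannot be run forward because no SD is stated. Solved backwards, SD = (2 − 0.3)/2.8016 × √(64/2) = 3.43 points. At one-sided 0.0125 it is 3.12. The figure is therefore consistent with a non-inferiority comparison of mean collapse. Nothing in it refers to oxygenation or PPCs.

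**2. Precision for PPCs at 18%.** SE = √(2 × 0.18 × 0.82/n).
- n = 64: SE = 0.0679; half-width 1.96 × 0.0679 = 0.133
- n = 70: SE = 0.0649; half-width 0.127

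With 18% observed in both arms and 64 per arm, the CI would still include an excess of 13.3 points (18% against about 31%).

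**3. Power for non-inferiority on PPCs.** Power = Φ(margin/SE − 1.96).

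| Assumed margin | n = 64 | n = 70 | n per arm for 80% power |
|---|---|---|---|
| 5 points | 11% | 12% | 927 |
| 10 points | 31% | 34% | 232 |
| 15 points | 60% | 64% | 103 |
| 20 points | 84% | 87% | 58 |

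Check for 10 points: 2 × 0.18 × 0.82 × 2.8016²/0.10² = 231.7, so 232.

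**4. Smallest PPC margin testable with 80% power.** Margin = 2.8016 × SE.
- 18% rate: 0.190 (n = 64), 0.182 (n = 70)
- 10% rate: SE = √(2 × 0.10 × 0.90/64) = 0.0530, margin 0.149 (n = 64); 0.142 (n = 70)

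At 18%, the testable margin is as large as the event rate itself.

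**5. What the listed tests would show.** Suppose the true rates were 28% (Cstat) and 18% (EIT), with 64 per arm. The pooled rate is 0.23, the null SE is √(2 × 0.23 × 0.77/64) = 0.0744, and the SE under the alternative is √((0.18 × 0.82 + 0.28 × 0.72)/64) = 0.0739. Power = Φ((0.10 − 1.96 × 0.0744)/0.0739) = 27%, so the chi-square test would be non-significant 73% of the time. Exact enumeration of Fisher's test gives 80%.

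**6. Oxygenation.** This is continuous and no SD is given, so only SD units are possible. Smallest margin = 2.8016 × √(2/n) = 0.50 SD (n = 64) or 0.47 SD (n = 70). The CI half-width is 1.96 × √(2/n) = 0.35 or 0.33 SD. Whether a margin of that size would be acceptable cannot be judged from the article.

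**The case against.** The best defence is that the sample size section and the first paragraph of the Discussion already confine the formal test and the power claim to collapse. The PPC claim then rests on one Background sentence. Secondary outcomes normally have no sample size of their own, and margins for them could sit in an analysis plan that is not shown. The article also plans 95% CIs and relative risks as well as P values. This is fair, and it is why the opening of the Discussion needs no change. It does not remove the conflict. The article states these outcomes as part of the hypothesis to be verified, and an analysis plan could not supply a PPC margin much below 18 points that 140 patients could test with 80% power at the 18% rate.

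The 18% figure is a background upper value for obese patients in general, not a rate for this population and composite endpoint. That also stands, but at 10% the smallest testable margin is still about 15 points with 64 per arm.

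A reader might infer three stronger things that the document does not support:

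- **That a non-significant P value will be reported as non-inferiority.** No section says so. The risk is one of misreading.
- **That the trial is too small for oxygenation.** A margin of about 0.5 SD could be tested. What is missing is the margin.
- **That the oxygenation comparison is biased towards no difference because the post-titration blood gas follows a recruitment maneuver given to both arms.** The article gives no interval or figure to support this. Its own Discussion says PEEP after recruitment helps prevent collapse from re-forming, so the sample may still reflect each arm's PEEP.

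**Conclusion.** The point holds in this form. The Background claims non-inferiority on three outcomes and the closing Discussion on two, while the design provides a margin and a sample size for one. The analyses listed cannot establish non-inferiority on oxygenation or PPCs.

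For PPCs the shortfall is large: ±13 points of uncertainty and about one chance in three of excluding a 10-point excess if the arms are truly equal. These figures rest on an assumed 18% rate in both arms, an assumed margin and normal approximations. For oxygenation the conclusion is limited to the absent margin. The primary comparison of lung collapse is not affected. The differing rank of PPCs is a labelling inconsistency on which no stated analysis depends.

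**What to change.** - In the last paragraph of the Background and the closing paragraph of the Discussion, restrict the non-inferiority hypothesis and conclusion to EIT-measured lung collapse, in line with Sample size calculations and the opening of the Discussion.
- State that oxygenation and PPCs will be reported as between-group estimates with 95% CIs, and that no non-inferiority claim will be made on them.
- As a minor tidy-up, give PPCs the same rank in the Abstract and in Study endpoints.

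No change is needed to the opening paragraph of the Discussion or to the timing of the blood gas samples. Moving a sample during recruitment would split the oxygenation data for a benefit that cannot be quantified.

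The cost is wording and a narrower claim: the trial could say that Cstat titration is not inferior for collapse, and could only describe oxygenation and PPCs. Keeping the PPC claim would instead need a justified margin and, for 10 points at the assumed 18% rate, 232 per arm (464 in total) before any allowance for dropout.

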## Methods/design

### Objectives and design

This parallel, two-arm, single-center, prospective, single-blind (investigator-initiated, assessor-blinded), randomized, controlled trial tests the hypothesis that individualized PEEP titration guided by optimal Cstat is a convenient and feasible lung-protective strategy for obese patients at moderate to high risk for PPCs undergoing laparoscopic surgery. 140 patients will be randomly divided into one of two different groups (see Consolidated Standards of Reporting Trials [CONSORT] diagram, Fig. 1).

**Fig. 1 Fig1:**
[figure not shown]
Consolidated Standards of Reporting Trials (CONSORT) diagram for this trial. *PEEP* positive end-expiratory pressure, *iPEEP* individual PEEP, *COPD* chronic obstructive pulmonary disease, *ICU* intensive care unit, *ASA* American Society of Anesthesiologists classification, *PaO*_*2*_ partial pressure of arterial oxygen, *FiO*_*2*_ inspiratory fraction of inspired oxygen, *EIT* electrical impedance tomography, *PPCs* postoperative pulmonary complications

This trial will be conducted at Beijing Friendship Hospital Affiliated to Capital Medical University. The study conforms to the CIOMS Principles of the International Guidelines for Biomedical Research Involving Human Subjects and the WMA of the Declaration of Helsinki. The study has obtained ethics approval from the Ethics Committee of Beijing Friendship Hospital Affiliated to Capital Medical University. (The approval number is 2020-P2-145-01) and has been registered in the Chinese Clinical Registry (Chictr) (registration number: ChiCTR2000039144).

### Blinding, data collection, randomization, and record-keeping

This is a single-blind randomized clinical trial. Demographic parameters, intraoperative data, postoperative clinical status, fluid balance, hemodynamic variables, respiratory parameters, anesthesia data, laboratory results, and hygienic indicators will be recorded onto the case report forms (CRF). The information of lung collapse calculated by EIT will be stored in the computer and named with an anonymous number.

All participants meeting the inclusion criteria will be randomized to the Cstat-PEEP group or the EIT-PEEP group in a ratio of 1:1. Randomization will be implemented via a computer-generated blocked randomization form, with 35 blocks of four patients per block. The assignment will proceed with opaque, sealed, and numbered envelopes. Subjects shall be enrolled and allocated in numerical order. All original records (CRF and associated correspondence) will be archived and safeguarded for 10 years and then destroyed, as required by hospital standards.

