### Standard procedures

To avoid interfering the trial intervention, components of perioperative anesthesia care (involving general anesthesia, postoperative analgesia, and fluid management) are performed by a fairly fixed team of anesthesiologists in accordance with the clinical routine. The following strategies are recommended:
Before surgery, all patients need a thorough assessment of the airway, performed on the basis of 12 predictors of a difficult airway. When more than three of the predictors are present, endotracheal intubation is performed when patients are awake or after slow induction while maintaining spontaneous breathing should be taken into consideration. Adequate equipment, personnel, and medicine required for artificial airway establishment should be prepared in advance (see Additional Table 1: Predictors of Difficult Airway).According to clinical routine, upon admission to the operation room, patients’ following parameters are monitored: electrocardiogram, non-invasive blood pressure, BIS, pulse oximetry, and urine output. Invasive arterial blood pressure is continuously measured after the insertion of an arterial line into the radial or dorsal pedis artery under regional anesthesia.After intravenous and arterial catheterization, an EIT belt will be placed at the fifth intercostal space, and continuous EIT monitoring (PulmoVista 500, Drager) will be started.For patients without predicted difficult airway, anesthesia induction is performed using rapid sequence induction: 0.05mg/kg midazolam is given to patients 15 min before induction; sufentanil, etomidate, rocuronium, or cisatracurium are used for induction. Mechanical ventilation is initiated after endotracheal intubation.Total intravenous anesthesia is applied for the maintenance of anesthesia with propofol and remifentanil.Intraoperative hemodynamics is managed in accordance with surgical procedure and blood loss.Performing postoperative analgesia to ensure a VAS pain score<3. Regional anesthesia or neuraxial block should be applied whenever indicated.Postoperative physiotherapy involving early mobilization and stimulation of cough along with deep breathing exercises should be performed.

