### Study dropouts

As participation in the study is voluntary, all subjects are free to withdraw their consent to participate in the trial at any time and for any reason without any further treatment or any consequences. Moreover, participation of any subjects could be terminated by an investigator at any time, if he or she believes it is in the best interest of the subject. We shall document the reasons and circumstances of the study discontinuation in the CRF.

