### Trial status

We enrolled the first participant of the trial on November 15, 2020, the protocol version is the first version, and the version number is V1.0/2020.06.26. We will complete the recruitment on September 17, 2022. This trial is still ongoing.

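### Fixed blocks of four, used in order at a single centre, let anyone at enrolment who follows past allocations deduce up to a third of assignments in advance

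*Protocol article*

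**What the plan says.** In the protocol article, the section *Blinding, data collection, randomization, and record-keeping* says that patients are "randomized to the Cstat-PEEP group or the EIT-PEEP group in a ratio of 1:1" from a computer-generated list, "with 35 blocks of four patients per block". On concealment it says: "The assignment will proceed with opaque, sealed, and numbered envelopes". On order of use: "Subjects shall be enrolled and allocated in numerical order". No stratification or variation in block size is described.

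*Objectives and design* describes the trial as "single-center, prospective, single-blind (investigator-initiated, assessor-blinded"). *Intervention* sets out two visibly different titrations. The EIT arm steps PEEP down from 20 cmH2O every 40 s. The Cstat arm steps it up from 5 cmH2O with 3 min at each level. *Standard procedures* says that perioperative anaesthesia care is "performed by a fairly fixed team of anesthesiologists". *Study population* places screening and recruitment at the routine preoperative evaluation.

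*Trial status* gives a first enrolment on 15 November 2020 and adds: "We will complete the recruitment on September 17, 2022". The article appeared on 15 October 2021, so by its own dates recruitment was still open.

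**The concern.** Each element is common on its own. The difficulty is the combination: one known block size, one sequence in one centre, strict order of use, and arms that the treating staff can tell apart. A sealed envelope hides the next card, but it does not hide what follows from the cards already opened. In a 2:2 block of four the last assignment always follows from the first three, and the third sometimes follows from the first two.

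Someone who knows the next arm can influence which patient takes that place, or when. This acts at enrolment, before any outcome is measured, so assessor blinding does not remove it. In a non-inferiority comparison, placing lower-risk patients in the Cstat arm would push the result towards a false conclusion of non-inferiority.

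**Working it through.** **Inputs from the protocol article.** Blocks of four, 35 blocks, 1:1 (*Blinding, data collection, randomization, and record-keeping*). Margin of 2 percentage points, expected means of 6.5% and 6.2%, alpha 0.025, 80% power, 64 evaluable per arm (*Sample size calculations*).

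**The plan's own figure.** 35 × 4 = 140, which matches the planned total.

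**Assignments deducible with certainty.** A 2:2 block has 6 equally likely orderings.
- Position 4 is always determined: 1 per block.
- Position 3 is determined when the first two match, with probability 1/3.
- Total: (1 + 1/3) / 4 = 1/3, and 140 × 1/3 = 46.7, or about 47 patients.

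**Best-guess accuracy.** Guessing the arm with more places left succeeds with probability 1/2, 2/3, 2/3 and 1 at positions 1 to 4. The mean is (1/2 + 2/3 + 2/3 + 1) / 4 = 17/24 = 70.8%, against 50% by chance.

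**Illustration of what steering could do.** The article gives no SD, so one has to be assumed. Taking 0.025 as one-sided, the SD that yields 64 per arm is (2 − 0.3) × √(64/2) / (1.96 + 0.84) ≈ 3.4. The article calls its 0.025 two-sided. Read literally (one-sided 0.0125), the implied SD is about 3.1. The figures below use 3.4 and one-sided 0.025.

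Suppose every determined place is steered by δ points, towards less collapse in the Cstat arm and more in the EIT arm. One third of each arm is affected, so:
- bias = (1/3 + 1/3) × δ = 0.667 δ
- SE = 3.4 × √(2/64) = 0.601
- error at a true difference of 2 = P(Z > 1.96 − bias/SE)

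| Shift δ (points) | Bias (points) | Share of margin | One-sided error |
|---|---|---|---|
| 0 | 0 | 0% | 2.5% |
| ±0.1 | 0.07 | 3% | 3.2% |
| ±0.25 | 0.17 | 8% | 4.6% |
| ±0.5 | 0.33 | 17% | 8.0% |
| ±1.0 | 0.67 | 33% | 19.7% |

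For the bias alone to equal the margin, δ would have to be 2 / 0.667 = 3.0 points on every determined place, or 3.0 / 3.4 ≈ 0.9 SD.

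**Effect of other block schemes.** Fixed sizes were enumerated. The mixed schemes were simulated (400 lists of 140) for an observer who knows the possible sizes but not their order.

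| Scheme | Known with certainty | Best guess correct |
|---|---|---|
| Fixed 4 (as planned) | 33.3% | 70.8% |
| Fixed 6 | 25% | 68.3% |
| Fixed 8 | 20% | 66.6% |
| Random 4/6 | 5.3% | 69.2% |
| Random 4/6/8 | 2.3% | 67.9% |

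Random 4/6/8 leaves about 140 × 0.023 ≈ 3 assignments certain in advance. It removes most certainty but little guessing.

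**The case against.** The strongest reply is that the mechanism needs a person whom the article does not describe. Steering requires someone who accepts or schedules patients and also knows the running order of past allocations. The article places recruitment at the preoperative evaluation and gives the anaesthesia team the perioperative care. It does not say that this team recruits, holds the envelopes or follows the sequence, and who does so is a detail that a condensed article may leave to the full protocol. This stands, and it is why one third is an upper bound. It does not remove the point, because the fixed block size is a stated rule and nothing stated stops the deduction.

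The error rates are also worst cases. They assume that every determined place is recognised, that all are steered in the same direction, and that an enroller can foresee EIT-measured collapse before surgery. That stands too. The smaller shifts in the table show how quickly the effect shrinks.

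Publication of the block size can have informed staff only from October 2021, about half-way through the planned recruitment period. Staff could, however, have known the size from running the trial.

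Three stronger readings are tempting, and the documents do not support them:
- *Operators see every allocation.* They see the patients they treat, and a largely stable team does not mean that one person sees all 140.
- *A small shift would use up the 2-point margin.* That would take about ±3 points on every determined place. Modest shifts raise the error rate instead.
- *The investigator's discretion to withdraw patients belongs to this problem.* The rule that "participation of any subjects could be terminated by an investigator at any time" acts after enrolment, whatever the block size, and varying the blocks would not change it.

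**Conclusion.** The point holds as a predictability weakness in a stated design rule. Up to 33.3% of assignments (about 47 of 140) can be deduced and 70.8% guessed. Both figures are exact for 2:2 blocks of four, on condition that someone at enrolment knows the block size and follows the allocations in order. Sealed envelopes and assessor blinding leave this open.

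Bias in the result is a risk and has not been shown. The rise in one-sided error from 2.5% to between 4.6% and 19.7% for shifts of ±0.25 to ±1.0 points rests on the assumed SD, on 64 per arm and on consistent steering of every determined place. Because a standard and cheap change lowers the risk, it should be made while part of the list is unused.

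**What to change.** For patients not yet randomised:
- Regenerate the list with randomly varied block sizes, for example 4, 6 and 8, starting at the end of a completed block of four.
- Keep the sizes from everyone who screens, enrols or ventilates patients, and leave them out of public documents until recruitment closes.
- Open each envelope only once enrolment is final. *Standard procedures* and *Intervention* describe the same handling in both arms until titration after pneumoperitoneum, so opening just before titration is feasible.

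Since best-guess accuracy falls only to about 68%, varied blocks are not enough alone. Late opening matters, and where staffing allows, people who know past allocations should be kept out of eligibility and scheduling decisions.

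The cost is a short amendment, a new list and re-stuffed envelopes. The final arms may differ by a few patients: at most four if recruitment stops inside a block of eight, which is half the largest block. Assignments already made cannot be changed, so the benefit is limited to the remaining patients.
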